## Abstract

**Introduction::**

Pancreatic cancer is one of the most lethal malignancies worldwide. Most patients are diagnosed at an advanced stage, which leads to a poor prognosis and a low survival rate. At present, treatment options for pancreatic cancer are limited, so it is vital to explore new treatments and strategies. Traditional Chinese medicine (TCM) is an important method for cancer prevention and treatment in China. We will conduct a multicenter, prospective cohort study to evaluate the survival and quality of life of patients with advanced pancreatic cancer treated with integrated traditional Chinese and Western medicine, further refine the core pathogenesis of TCM for pancreatic cancer, form a core prescription, and provide clinical data support for the clinical plan of integrated treatment of pancreatic cancer using Chinese and Western medicine; this will aid in the development of the best comprehensive treatment plan for patients.

**Methods and analysis::**

This study will recruit patients with stage 3 to 4 pancreatic cancer in 12 medical units from April 2019 to June 2020. Patients will be divided into a Western medicine treatment group and an integrated traditional Chinese and Western medicine treatment group, with a total of 148 patients. Overall survival is the main efficacy index, while the secondary efficacy indexes are progression-free survival, tumor markers, TCM symptom grading scale, quality of life assessment, Eastern Cooperative Oncology Group (ECOG) score, and imaging assessment. A follow-up will be performed every 6 weeks ±1 week. The end point is the death of the patient or the end of the study (October 31, 2021). Statistical analysis will be performed using Statistical Packages of Social Sciences software (SPSS).

**Ethics and dissemination::**

This work was supported by Beijing Municipal Science and Technology Commission and approved by the ethics committee of Guang’anmen Hospital, China Academy of Chinese Medical Sciences (Approval No. 2019-016-KY). All patients will sign a written informed consent prior to data collection. The results will be disseminated through peer-reviewed journals and conference presentations and will be openly shared after completion of the trial.

**Trial Registration::**

The trial was registered with the Chinese Clinical Trials Registry (ChiCTR1900022632, pre-registration).

## Introduction

1

Pancreatic cancer is one of the most lethal malignancies worldwide. According to a GLOBOCAN report, there are an estimated 458,918 new cases, and there were 432,242 cancer deaths in 2018. Of those cases, one-fifth occurred in China.^[1]^ According to the China cancer registry data of 2014, it is the seventh leading cause of cancer death in either sex, with 92,000 new cases and 81,100 deaths each year.^[2]^ The mortality rate is closely related to the incidence rate and is increasing year by year.

So far, although some risk factors have been identified related to the occurrence of pancreatic cancer, such as smoking, diabetes, dietary factors, obesity, alcoholism, age, ethnicity, family history and genetic factors, *Helicobacter pylori* infection, and chronic pancreatitis.^[3]^ But the causes of pancreatic carcinoma are still not fully known.^[4]^ Pancreatic ductal adenocarcinoma (PDAC) is the most common type of pancreatic cancer, and it accounts for approximately 85% of pancreatic malignancies.^[5]^ Pancreatic cancer is insidious with atypical early symptoms. It often manifests as upper abdominal discomfort, lower back pain, indigestion, or diarrhea, and is easily confused with other digestive diseases. There are currently no standard procedures for screening patients at high risk for pancreatic cancer, and most patients have no symptoms before the disease progresses to an advanced stage. Most patients are in the advanced stage at the time of diagnosis, with a natural course of 4 to 6 months, which leads to a poor prognosis and a low survival rate. The global surveillance of trends in cancer survival during 2000 to 2014 shows that age-standardized 5-year net survival estimates were generally in the range of 5% to 15%, and in most countries it is no >15%. In fact, even France, Japan, New Zealand, and many other developed countries are below 10%.^[6]^

Pancreatic cancer treatment options are limited at present; surgery is still the first-line treatment for early pancreatic cancer and is considered to have the potential to result in a cure. Postoperative adjuvant chemotherapy, radiotherapy, and traditional Chinese medicine (TCM) treatment can significantly prolong the survival of patients,^[7–9]^ but only about 20% of patients have the opportunity to have an initial resection.^[10]^ The 5-year survival rate of patients with a complete resection is only 25%, and recurrence and metastasis remain the leading cause of death in most patients.^[11]^ The potential benefits of radiotherapy for locally advanced pancreatic cancer have been extensively studied, and palliative surgery is feasible for patients with locally advanced and metastatic pancreatic cancer but chemotherapy is still the main treatment. However, the efficacy of chemoradiotherapy is limited,^[12]^ so it is urgent to explore new treatment methods or treatment options.

Studies have shown that the median survival of patients with stage III/IV pancreatic cancer treated with Western medicine is 6 to 11 months,^[13,14]^ and the 1-year survival rate is only about 20%. TCM is an important method for cancer prevention and treatment in China. The clinical observation of 59 patients with advanced pancreatic cancer showed that intervention with TCM could prolong the median survival of stage III/IV pancreatic cancer for >2 months.^[9]^ Therefore, it is urgent to accelerate the formation of a clinical plan for the treatment of pancreatic cancer with integrated traditional Chinese and Western medicine.

## Objective and purpose

2

This study will conduct a multicenter, prospective cohort study to evaluate the survival and quality of life of patients with advanced pancreatic cancer treated with integrated traditional Chinese and Western medicine, further refine the core pathogenesis of TCM for pancreatic cancer, form a core prescription, and provide clinical data support for a treatment plan that integrates Chinese and Western medicine and enables the development of the best comprehensive plan for patients.

## Methods and analysis

3

### Study setting and design

3.1

This study is a multicenter, prospective cohort study on the clinical efficacy of integrated traditional Chinese and Western medicine in the treatment of pancreatic cancer. It was launched in April 2019 and is scheduled to end in October 2021 with enrollment to be completed by June 31, 2020. All cases will be collected at 12 medical units including Guang’anmen Hospital, China Academy of Chinese Medical Sciences, Henan Provincial Cancer Hospital, Jining No.1 People's Hospital, Jiangsu Provincial Hospital of Chinese Medicine, Zhejiang Provincial Hospital of TCM, Yueyang Hospital of Integrated Traditional Chinese and Western Medicine, Shanghai University of Traditional Chinese Medicine, Tongde Hospital of Zhejiang Province, Wangjing Hospital of CACMS, Xiyuan Hospital CACMS, Chongqing Cancer Hospital, Gansu Provincial Cancer Hospital, and Shanxi Provincial Cancer Hospital. A total of 148 patients will be admitted to the treatment group with Western medicine and the integrated treatment group with traditional Chinese and Western medicine. The study schema and the flow chart are presented in Fig. 1. Inclusion and exclusion criteria are presented in Table 1. Two investigators will be responsible for the follow-up of each participant at baseline and every 6 weeks ± 1 week, and the data collection schedule is presented in Table 2.

**Figure 1 F1:**
[figure not shown]
Study schema and flow chart.

**Table 1 T1:**
[figure not shown]
Patient inclusion and exclusion criteria.

**Table 2 T2:**
[figure not shown]
Data collection schedule.

### Participants

3.2

All patients fulfilling the inclusion criteria will be recruited, and those who meet one or more of the exclusion criteria will be refused.

### Shedding criteria

3.3

A researcher can decide to withdraw a patient from the study if:

1.The patient has an allergic reaction or serious adverse event.2.During the study, the patient has other complications and special physiological changes, and it is not appropriate to continue in the study.3.Subjects have poor compliance, or change their own drugs, or add non-specified combinations, especially those that have a greater impact on the study affecting the effectiveness and safety.

Subjects can quit on their own:

1.For whatever reason, the patient is unwilling or unable to continue the clinical research and makes a request to the doctor in charge to withdraw from the trial.2.The subjects do not explicitly withdraw from the study, but they will not receive medication or follow-up.

Treatment of shed cases

For cases of withdrawal from the trial or loss to follow-up, the investigator should actively take measures to complete the last follow-up to analyze treatment efficacy and safety. For all cases of abscission, a case report form (CRF) and the cause of abscission should be completed.

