### End point of observation

3.8

Patient death or the end of the study (October 31, 2021).

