#### Overall survival (OS)

4.1.1

The primary outcome of this study is OS, which is from enrollment to patient death or the end of the study (October 31, 2021).

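### Section 3.3 allows study exit after a serious adverse event or complication and asks only for a final follow-up, in conflict with an OS endpoint that runs to death or 31 October 2021

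*Protocol article*

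**What the plan says.** Protocol article, section 3.3 (Shedding criteria), introduces the investigator's list with "A researcher can decide to withdraw a patient from the study if". Item 1 is "The patient has an allergic reaction or serious adverse event". Item 2 covers cases where "the patient has other complications and special physiological changes, and it is not appropriate to continue in the study". What the patient leaves is the study; stopping a treatment is not distinguished from ending observation.

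Under the subject's own reasons, item 2 reads "The subjects do not explicitly withdraw from the study, but they will not receive medication or follow-up".

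For patients who withdraw or are lost, "the investigator should actively take measures to complete the last follow-up to analyze treatment efficacy and safety". A case report form and the cause are also completed. Nothing is said about ascertaining death after that.

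Section 3.8 (End point of observation) gives only "Patient death or the end of the study (October 31, 2021". Section 4.1.1 defines OS as the time "which is from enrollment to patient death or the end of the study (October 31, 2021". Neither names withdrawal as an exit. Section 4.3.4 (Data analysis) plans a log-rank test and the 25%, 50% and 75% survival times for each cohort. Section 5.2 (Limitations) intends to keep following survival beyond the end of the study, but does not say whether shed patients are included.

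**The concern.** In stage III/IV pancreatic cancer a serious adverse event or complication is plausibly a marker of approaching death; the Introduction puts the natural course of advanced disease at 4 to 6 months. If leaving the study also ends the search for a death date, these patients would enter the OS analysis censored at last contact, although their risk of death is higher than that of patients still under observation. The log-rank test and the survival quantiles assume that censoring is unrelated to prognosis.

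At stake are the absolute survival figures in both groups and, if withdrawal is uneven, the comparison between them. Withdrawal is at the discretion of an investigator who can know the treatment, so unevenness is possible. This is not a detail that an analysis plan can settle later: a death date that was never collected cannot be analysed. Nor does an observational cohort with a mortality endpoint need to stop recording vital status because of an adverse event.

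**Working it through.** **1. The sections side by side**

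| Place | What ends observation |
|---|---|
| 3.3 | Researcher may withdraw the patient from the study; a final follow-up is sought |
| 3.8 | Death or 31 October 2021 |
| 4.1.1 | OS runs to death or 31 October 2021 |
| 5.2 | Survival follow-up continues after study end; shed patients not mentioned |

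Sections 3.8 and 4.1.1 are met for a withdrawn patient only if vital status is still sought after withdrawal. Section 3.3 does not say that it is.

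**2. Inputs for an illustration of size**

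- From section 3.5: 1-year survival of 22% in the non-exposed group; 148 patients at 1:1, so 74 per group; dropout of 15%.
- From the study dates (enrolment April 2019 to June 2020, end October 2021): about 16 to 31 months of potential follow-up.
- Assumed, not in the documents: exponential survival; a share w of dying patients is withdrawn and censored on average 1 month before death; any split of w between groups. The plan's 15% is dropout from all causes. Applying all of it to patients near death is an assumption.

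**3. Closed-form approximation (lead time near zero)**

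Hazard λ = −ln(0.22)/12 = 0.126 per month. True median = ln 2/0.126 = 5.5 months. Replacing a share w of deaths by censoring just before death lowers the apparent hazard to (1 − w)λ. With w = 0.15:

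- apparent 1-year survival = 0.22^0.85 = 0.276
- apparent median = ln 2/(0.85 × 0.126) = 6.5 months
- hazard ratio, equal withdrawal = 0.85/0.85 = 1.00
- null hazard ratio (integrated/Western), 15% integrated and 5% Western = 0.85/0.95 = 0.89
- null hazard ratio, reversed split = 0.95/0.85 = 1.12

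**4. Simulation (74 per group, true 1-year survival 22% in both groups, mean lead 1 month, follow-up uniform on 16 to 31 months)**

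| Withdrawn, Western / integrated | 1-year survival, integrated | Median, integrated (months) | Null hazard ratio |
|---|---|---|---|
| 0% / 0% | 22% | 5.6 | 1.00 |
| 15% / 15% | 27% | 6.4 | 1.00 |
| 5% / 15% | 27% | 6.4 | 0.90 |
| 15% / 5% | 23.5% | 5.8 | 1.10 |

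The 5.6 months in the first row is an average over samples of 74; the exact value is 5.5.

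**5. Sensitivity**

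A separate large-sample run with 22 months of follow-up and a fixed 1.5-month lead gives 1-year survival of 24.9%, 26.6%, 28.5% and 32.6% at 10%, 15%, 20% and 30% withdrawn. At 15%, lengthening the lead from 1 to 3 months moves the estimate from 26.9% to 25.9%, so the share withdrawn matters more than the lead. With 15% in both groups the one-sided rejection rate at .05 stays near 5%. With 5% Western and 15% integrated it is about 13% to 15%; with the split reversed it is about 1.6%.

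**The case against.** The strongest reply is that the protocol never says these patients are censored. A reader might infer from section 3.3 that OS is definitely censored in the patients nearest death. The documents do not support that as a statement of fact. No censoring rule is given, withdrawal is discretionary, and sections 3.8, 4.1.1 and 5.2 can be read as following survival regardless. The request to complete a final follow-up can itself be read as an instruction to obtain outcome data. This stands, and the point is therefore conditional. It does not remove the conflict, because no section says that deaths are ascertained after withdrawal.

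A reader might also infer from item 2 of the subject list that stopping medication alone counts as shedding. The more natural reading is silent dropout, where the patient accepts neither treatment nor follow-up. Section 3.9 supports this: patients whose chemotherapy has ended move into the follow-up period. The wording needs only clarification.

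A third tempting inference is that the rule favours integrated treatment and inflates false positives. That depends wholly on an assumed imbalance, and the direction reverses with it. The simulation also fixes the groups at enrolment, whereas section 3.7 classifies patients after data collection by duration of TCM and number of chemotherapy courses, so an early withdrawal may never qualify for the integrated group. The simulation shows a plausible size and is not a prediction for this design.

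Finally, the analysis set and the censoring rule may properly sit in an analysis plan that is not shown. That is fair for the analysis. It does not answer the collection of death dates, which section 3.3 governs.

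**Conclusion.** The concern holds in conditional form. Section 3.3 permits exit from the study on grounds linked to deterioration and asks only for a final follow-up, while sections 3.8 and 4.1.1 allow observation to end only at death or 31 October 2021. If section 3.3 is followed and vital status is not pursued, censoring becomes informative for the primary endpoint and the loss cannot be repaired afterwards.

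If 15% of dying patients in each group were lost about 1 month before death, 1-year survival would be overstated by about 5 percentage points and median OS by about 0.8 months, with no effect on the hazard ratio. Bias in the comparison needs unequal withdrawal: a null hazard ratio of about 0.90 or 1.10 for a 15% against 5% split, depending on which group loses more. The shares, the split and the lead time are assumptions. The documents support the existence of the conflict, not a particular size or direction of bias.

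**What to change.** Reconcile sections 3.3, 3.8, 4.1.1 and 5.2 by separating stopping treatment from leaving follow-up:

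- State in section 3.3 that a serious adverse event, allergic reaction or complication does not end vital-status follow-up, which continues to death or 31 October 2021. Telephone contact is enough.
- State that only withdrawal of consent to follow-up ends it.
- State that these patients stay in the OS analysis with their true death date.
- Reword item 2 of the subject list to mean silent dropout, and say that stopping medication alone is not shedding.
- Say in section 5.2 that the intended survival follow-up includes shed patients.

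No treatment rule changes. The cost is protocol wording and a few telephone contacts, and section 5.2 already intends survival follow-up beyond study end.

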### Limitations

5.2

This study also has some limitations. The present study is a prospective cohort study with a small patient sample size. However, because of the lower incidence of pancreatic cancer relative to other cancers, the number of patients with advanced pancreatic cancer meeting the inclusion and exclusion criteria may be relatively small, which will result in a small sample size. Given the small sample size, the amount of data that can be collected from the integrated Chinese and Western medicine group may lead to results that are not as robust as would be feasible with a larger sample size. Because of the short study duration and funding constraints, only 148 advanced pancreatic cancer patients were eventually recruited. However, even after the end of the study, we will continue to follow the survival of subjects so as to more accurately analyze and evaluate the clinical efficacy of integrated Chinese and Western medicine in the treatment of pancreatic cancer.

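### Section 3.3 lets patients be withdrawn from the study without securing their vital status afterwards, although overall survival is meant to run to death or 31 October 2021

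*Protocol article*

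**What the plan says.** All references are to the protocol article.

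- **Section 3.3 (Shedding criteria), who decides and from what.** "A researcher can decide to withdraw a patient from the study if" one of three reasons applies. The withdrawal is from the study, not only from a treatment.
- **Section 3.3, the reasons.** The first is "The patient has an allergic reaction or serious adverse event". The second is that "the patient has other complications and special physiological changes, and it is not appropriate to continue in the study". The third begins "Subjects have poor compliance, or change their own drugs, or add non-specified combinations".
- **Section 3.3, what happens next.** For withdrawn or lost patients, "the investigator should actively take measures to complete the last follow-up to analyze treatment efficacy and safety". The case report form and the cause are also to be completed. No later survival contact is mentioned.
- **Section 3.8 (End point of observation).** "Patient death or the end of the study (October 31, 2021". Withdrawal is not listed.
- **Section 4.1.1 (Overall survival).** The primary outcome is OS, "which is from enrollment to patient death or the end of the study". Withdrawal is not listed here either.
- **Section 5.2 (Limitations).** "even after the end of the study, we will continue to follow the survival of subjects". Withdrawn patients are neither included nor excluded.

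**The concern.** In an observational cohort with OS as the primary outcome, every enrolled patient's death counts, whatever happened to the treatment. Section 3.3 does not secure that. A site that reads it as the end of contact stops collecting vital status at withdrawal; a site that works from Sections 3.8 and 4.1.1 carries on.

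If contact stops, OS has to be censored at the last visit. Kaplan-Meier curves, the log-rank test and Cox regression (all planned in Section 4.3.4 or implied by it) assume that censored patients have the same later risk as those still followed. In stage III/IV disease, with the 6 to 11 months' median survival given in the Introduction, a serious adverse event or a complication plausibly comes shortly before death, so the assumption may fail. An analysis plan cannot repair this, because the missing deaths would never have been collected.

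**Working it through.** **1. Passages side by side.** Section 3.3 sets a minimum at withdrawal: last follow-up, case report form, cause. Sections 3.8 and 4.1.1 set the end of observation at death or 31 October 2021. Nothing says which governs a withdrawn patient. The document states no rule that censors OS at withdrawal, and no rule that prevents it.

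**2. Inputs for sizing the risk.** The document has no figure on this point to reproduce, so the size is an illustration.

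- From the document: 148 patients at 1:1, so 74 per group; a 15% dropout rate (Section 3.5, no split by group); a one-sided test at 0.05 for major efficacy indicators (Section 4.3.4); enrolment April 2019 to June 2020 and study end in October 2021, so about 16 to 30 months of possible follow-up.
- Assumed: exponential survival with an 8-month median (inside the 6 to 11 months cited); each withdrawn patient is censored 1 month before death; the withdrawal fractions in each group; no true difference between groups.

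**3. Absolute survival.** True 1-year survival is 0.5^(12/8) = 0.354. If a fraction f of patients is censored just before death, the observed death hazard falls to about (1 − f) times the true one. With f = 0.15:

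- 1-year survival reads about 0.354^0.85 = 0.413.
- The median reads about 8/0.85 = 9.4 months.

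Simulation with the 1-month lag gives about 41% instead of 35%, and 9.3 instead of 8.0 months.

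On the protocol's own planning rates, with censoring spread over 0 to 3 months before death and 15% withdrawn, a true 22% reads 26.7% and a true 45% reads 50.2%. Each is about 5 points too high, and the difference between them stays at 23.5 points against a true 23.

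**4. Group comparison under no true effect.** By the same approximation, HR ≈ (1 − f₁)/(1 − f₀), where f₁ is the fraction withdrawn in the integrated group and f₀ in the Western medicine group. The simulated columns come from several thousand null trials per scenario, with 74 patients per group. The false-positive rate is for a one-sided log-rank test favouring the integrated group.

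| Withdrawn, integrated vs Western | Approximate HR | Simulated HR | One-sided false-positive rate |
|---|---|---|---|
| 15% vs 15% | 0.85/0.85 = 1.00 | 1.00 | about 5% |
| 15% vs 5% | 0.85/0.95 = 0.89 | about 0.91 | about 13% |
| 20% vs 5% | 0.80/0.95 = 0.84 | about 0.85 | about 21% |
| 5% vs 15% | 0.95/0.85 = 1.12 | about 1.11 | below 5% (bias reversed) |

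Repeat runs move the hazard ratios by about 0.01 and the error rates by about 1 point. Spreading the censoring over 0 to 3 months before death gives nearly the same results (0.90 and 13% for 15% vs 5%; 0.86 and 20% for 20% vs 5%), so they do not hinge on the 1-month lag.

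**The case against.** A reader might infer that the protocol removes these patients, allows them a single last visit and censors OS just when death is most likely. The text does not support that.

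- Withdrawal is at the researcher's discretion, and the second reason also requires that continuing be inappropriate.
- The last follow-up is a minimum. Later survival contact is not forbidden, and Section 5.2 plans survival follow-up of subjects beyond the study end.
- Censoring at withdrawal is written nowhere; Sections 3.8 and 4.1.1 point the other way.
- The link to imminent death is plausible for serious adverse events and complications. Nothing in the document supports it for allergic reactions, poor compliance or drug changes.

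The adverse scenarios also combine informative withdrawal with a three- to four-fold difference between groups, and the document gives data on neither. Milder assumptions give less: 10% against 7% yields an HR of 0.97 and a 7.2% false-positive rate; 15% against 5% with half the withdrawals unrelated to prognosis yields 0.95 and 8.2%. With equal withdrawal the comparison is unbiased. A difference in withdrawal does no harm by itself; it must also be informative.

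All of this stands, and it limits the point to a gap that can bias OS, not a rule that must. It does not close the gap. Section 5.2 does not say whether withdrawn patients count as subjects. Equal withdrawal cannot be taken for granted either: under Section 3.7 groups are formed after data collection, and the integrated group needs at least 12 weeks of TCM, so the timing of withdrawal can affect which group a patient enters.

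**Conclusion.** The point holds as an unreconciled gap. Section 3.3 allows withdrawal from the study and does not secure vital status afterwards, while Sections 3.8 and 4.1.1 need it to death or 31 October 2021. If sites stop contact, absolute survival is overstated, by about 6 points at 1 year (41% against 35%) when 15% leave a month before death and the median is 8 months.

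Bias in the treatment comparison is conditional on informative withdrawal that differs between groups. Its direction is unknown: the null HR is about 0.91 for 15% against 5%, 1.00 for equal fractions and about 1.11 for 5% against 15%. The withdrawal fractions by group, the lag before death and the exponential shape are assumptions. The gap should be corrected in the protocol itself, because deaths that were not collected cannot be restored at analysis.

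**What to change.** Reconcile Sections 3.3, 3.8 and 4.1.1 by adding to Section 3.3 that:

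1. withdrawal does not end survival follow-up;
2. the vital status of every enrolled patient is collected to death or 31 October 2021, unless the patient withdraws consent for follow-up itself;
3. withdrawn patients stay in the OS analysis and are not censored at withdrawal.

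The list of withdrawal reasons and the definition of exposure can stay as they are; protecting OS does not require changing them. The sample size is unaffected. The cost is a short protocol amendment and a few more vital-status contacts, for which Section 5.2 already foresees the means.
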